#### Settings and Recruitment

We will recruit from SFVAMC and JMMC inpatient units using two recruitment strategies. First, we will inform the cardiologists and nurses in the cardiac units at the hospital sites about the study so they can identify patients who meet eligibility criteria. A patient-friendly handout will be made available for the health care team to give to interested participants. Second, we will obtain a daily list of patients who had PCI and their electronic medical records will be screened for eligibility in the study using a checklist to examine the inclusion and exclusion criteria. Participants who agree to participate will provide written informed consent.

#### Randomization

Group assignment will be generated by random allocation sequence using random blocks stratified within recruitment site (SFVAMC or JMMC) of either three or six, which will be prepared by the study biostatistician. The research team will assign patients to their groups by distributing presealed envelopes in consecutive, numbered order. Due to the nature of the study design, the research team and participants cannot be blinded to the intervention once group assignment is determined.

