#### Sample Size Estimation

We plan to enroll 225 total participants (75 participants per group). Allowing for a 15% attrition rate over the 12-month study, we conservatively estimate that this recruitment target will result in a total sample size of n=192, which will give 86% power to detect a medium effect size (half-SD difference) between at least one treatment group and the control group using Dunnett’s method to adjust for multiple comparisons. This sample size would give more than 95% power to detect an effect size of d=0.69, as found in our previous clinical trial [33]. Analysis of the longitudinal data points with mixed-effects models will confer additional power.

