#### Sample

The convenience sample will consist of 159 male and female Veterans from SFVAMC and 66 female participants (29% of sample) from JMMC. A sample size of 225 is considered to be feasible considering the number of post-ACS/PCI patients who are treated at both institutions. We have incorporated a 29% oversample of women to ensure a sufficient sample size to examine subgroup differences in intervention effects, given the low enrollment of female Veterans in Veterans Health Administration (6%) [38]. Inclusion criteria include: (1) >21 years of age, (2) recent ACS or PCI within one week, and (3) new antiplatelet (thienopyridine) prescription. Exclusion criteria are: (1) cognitive impairment, and (2) lack of English proficiency/literacy. For the process evaluation, we will recruit a subset of 10 participants from each experimental group (text messaging and mobile app; total n=20) for in-depth individual interviews.

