#### Intervention

We will conduct an RCT with random assignment to one of three groups: (1) text messaging, (2) mobile app, or (3) website-control, for a total of 12 months. Both intervention groups will also be offered the patient education website that the control group will be given. The *text messaging group* will receive text messages with content and frequency informed by Aim 1. We will use the Veterans Affairs (VA) *Annie* text messaging program. For non-Veteran females, we will use a text messaging program from CareSpeak Communications. The *app group* will use the preferred app that is selected in Aim 2. The major purpose of the app is to remind participants to take medications; however, the app will likely include other features such as providing educational messages. The *website group* will be offered the American Heart Association patient education website (My Life Check - 7 Steps To Healthy Living) and will serve as an active control group [43]. The website will be offered to participants in all three groups. The *7 small steps to big changes* are to manage blood pressure, control cholesterol, reduce blood sugar, get active, eat better, lose weight, and stop smoking.

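### Published blocks of three or six for three open arms let anyone who tracks past assignments guess the next arm about 58% of the time, an avoidable risk of selection bias

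*Protocol article*

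**What the plan says.** All of the following is in the protocol article.

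- **Arms and sizes.** The Intervention section describes "random assignment to one of three groups". The Sample Size Estimation section implies equal allocation: "We plan to enroll 225 total participants (75 participants per group". The Sample section splits the strata into "159 male and female Veterans from SFVAMC and 66 female participants (29% of sample) from JMMC".
- **Sequence.** The Randomization section specifies "random blocks stratified within recruitment site (SFVAMC or JMMC) of either three or six", "which will be prepared by the study biostatistician".
- **Assignment.** The same section says: "The research team will assign patients to their groups by distributing presealed envelopes in consecutive, numbered order".
- **Blinding.** It adds that "the research team and participants cannot be blinded to the intervention once group assignment is determined".
- **Recruitment.** The Settings and Recruitment section says: "We will recruit from SFVAMC and JMMC inpatient units using two recruitment strategies". These are referral by ward staff and screening of a daily list of PCI patients.
- **Timing.** The Results section puts the start of the RCT in early 2018, after the article was written. The block sizes are therefore public before the first envelope is opened.

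**The concern.** Every block of three holds exactly one card per arm, and every block of six holds two. Sealed, numbered envelopes hide the next card. They do not hide what can be inferred from earlier cards once allocation is open and the sizes are known. There are only two strata, so the history needed for that inference is short and easy to follow.

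If the people who approach patients also know that history, they can favour or discourage an approach according to the likely next arm, even without intending to. The outcome is patient behaviour, and a recruiter may be able to sense a patient's motivation at the bedside. Expected adherence could then differ between arms before any intervention starts. Electronic pill-cap measurement would record that difference faithfully and could not remove it, and later analysis could not reliably do so either.

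**Working it through.** **Yardstick.** The article gives no figure for predictability. Its design target is a half-SD difference with 86% power at n=192. That figure reproduces: 225 × 0.85 = 191.25, about 64 per arm. A simulated two-sided Dunnett test at 0.05 with d = 0.5 in both active arms gives 86.1%. The power figure is not affected by this point; it only supplies 0.5 SD as the scale.

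**Inputs.** Three arms, 1:1:1; strata of 159 and 66; block sizes 3 and 6. The mixing probability is not given, so 1/2 each is assumed, with a range of 1/3 to 2/3.

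**Prediction rule.** The guesser knows the sizes and all past assignments in the stratum but not the block boundaries. Let a state s be the cards left in the current block, with weight w(s), n(s) cards in total and n_j(s) of arm j.

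- P(next = j) = Σ w(s) · n_j(s)/n(s)
- After arm j is seen, each w(s) is multiplied by n_j(s)/n(s), that card is removed and the weights are rescaled.
- An empty state becomes a new block of 3 or 6.
- The guess is the arm with the largest probability.

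**Example by hand.** The list starts A, B.

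- Likelihood under a block of 3: 1/3 × 1/2 = 5/30.
- Likelihood under a block of 6: 2/6 × 2/5 = 4/30.
- Posterior for a block of 3: 5/9.
- P(next = C) = 5/9 × 1 + 4/9 × 2/4 = 7/9, or 78%.

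**Simulated lists (1,500 per stratum, sizes equally likely and known).**

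| Block sizes | Correct guess, N=159 / N=66 | Certain, N=159 / N=66 |
|---|---|---|
| 3, 6 (plan) | 57.7% / 57.6% | 8.8% / 8.6% |
| 6, 9, 12 | 52.8% / 52.5% | 2.5% / 2.4% |
| 9, 12, 15 | 50.8% / 50.4% | 1.9% / 1.8% |
| No blocking | 33.3% | 0% |

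Under the plan's sizes, one arm can be ruled out for about 22% of assignments. Certain assignments number about 0.088 × 159 + 0.086 × 66 ≈ 20 of 225. Varying the mixing probability of block 3 from 1/3 to 2/3 gives 57–59% correct and 6–11% certain. For comparison, fixed blocks of known size give 61.1% correct and 33% certain (size 3: (1/3 + 1/2 + 1)/3 = 0.611), or 56.1% and 20% (size 6).

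**From guessing to bias.** Let p be the guesser's probability that control is next. Bias is the mean shift in expected adherence among active patients minus that among control patients. The 0.25 SD shift is an assumption; the documents give no such figure.

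| Steering rule | Bias at 0.25 SD | Share of 0.5 SD | Bias at 0.10 SD |
|---|---|---|---|
| ±0.25 only when the next arm is certain | 0.04 | 8% | 0.016 |
| Graded: −0.25 × (p − 1/3)/(2/3) | 0.11 | 22% | 0.044 |
| Full ±0.25 whenever p differs from 1/3 | 0.22 | 44% | 0.088 |

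The last column is the first multiplied by 0.10/0.25, since the bias is proportional to the shift. Under the third rule, sizes 6, 9, 12 give 0.17 SD and sizes 9, 12, 15 give 0.15 SD, even if those sizes are known.

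**The case against.** The other side has several sound arguments.

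- **The safeguards are real.** The biostatistician makes the list, the envelopes are presealed and used in order, and the block size varies at random. Mixing helps: about 9% of assignments are certain, against 20% or 33% with a fixed size. A reader might infer that upcoming assignments are known. More than 90% are not; they are only guessable at better than chance.
- **The worst case needs an unusual recruiter.** It takes someone who tracks every assignment, updates probabilities exactly and acts on any departure from 1/3. A reader might take 0.22 SD as the likely bias. The documents do not support that: the shift is assumed and the milder rules give 0.04 or 0.11 SD.
- **Room to steer is limited.** Screening uses a daily PCI list and an eligibility checklist, and entry requires an event within one week. Holding a patient back for a better envelope is hard. Selective or half-hearted approach remains possible.
- **Recruiters and assigners are not stated to be the same people.** The Settings and Recruitment section uses the first person plural, and the Randomization section names the research team. The only definition of that team (principal investigator and research assistant) is in the Aim 1 Recruitment section, for the focus groups. The overlap is a reasonable inference, no more.
- **Envelope handling detail is no finding.** Opening order, time logs and custody are commonly left to the full protocol.
- **Larger blocks alone are a partial remedy.** They move guessing only from 58% to 51–53%.

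What remains is that the article itself fixes the smallest block sizes and publishes them before enrolment. Sealed envelopes do not answer that.

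**Conclusion.** The point holds as an avoidable design weakness. It is not an internal contradiction and not evidence of bias. Given known sizes, open allocation and a tracker of past assignments within a site, the next arm can be guessed about 58% of the time and about 9% of assignments are certain. This changes little over plausible mixing probabilities and is the same at both sites.

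The step from predictability to bias rests on two unverified conditions: that those who recruit know the assignment history, and that they act on it. If they did, the bias at an assumed 0.25 SD shift would lie between 0.04 and 0.22 SD depending on the steering rule, and would scale with the shift. The change is worth making because it is cheap before enrolment and the damage, if it occurred, could not be reliably repaired afterwards.

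**What to change.** Before RCT enrolment opens:

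1. Have the biostatistician regenerate the list for both sites with larger, randomly mixed blocks that exclude three. For example, 6, 9 and 12 give about 53% correct guesses and 2.5% certain even if known; 9, 12 and 15 give about 51% and 2%.
2. Keep the new sizes unpublished and unknown to everyone who screens, consents or assigns. The text would say only that block sizes vary at random and are held by the biostatistician. This step addresses the mechanism most directly, since larger blocks alone lower the guess rate only moderately.

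Cost: one new list and one changed sentence. A site that stops mid-block could end with a somewhat larger imbalance. The largest possible gap between two arms at a site is one arm's share of the block: 12/3 = 4 or 15/3 = 5 patients, against 6/3 = 2 now.

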#### Baseline Data Collection

After written consent is obtained, we will collect clinical data by reviewing electronic medical records. Participants will complete the following baseline questionnaires: (1) sociodemographic information and medical history, (2) mobile phone use, and (3) Mini-Cog Test [39]. All instruments and frequency of administration are described in Table 2.

**Table 2 table2:** Measurement of medication adherence with intervals.

Measure	Description	Rationale	Months					
			0	1	3	6	9	12
Key Primary Endpoint								
Medication Event Monitoring System (MEMS) [40]	Electronic pill caps time stamp when the bottle is opened, correlating with intake of medication. Primary outcome is percentage (0-100%) of prescribed doses taken	Most objective, noninvasive method and considered the “gold standard”		x		x		x
Secondary Patient-Reported Endpoints								
MEMS [40]	Percentages (0-100%) of (1) days correct doses are taken, and (2) doses taken on schedule	Most objective, noninvasive method and considered the “gold standard”		x		x		x
Morisky Scale [41,42]	Eight-item Morisky Medication Adherence Scale (MMAS-8) self-reported questionnaire on adherence behavior for a range of scores 0-8, with higher scores indicating poor adherence (Cronbach alpha=0.83).	Most popular scale and well-validated instrument with high reliability	x	x		x		x
7-Day Recall	One item asking how many days in the past week patient remembered to take medications. Final outcome is a percentage (0-100%).	Most commonly used method in the clinical setting	x	x		x		x
Secondary Objective Endpoints								
Veterans Affairs Corporate Data Warehouse (Veterans)	Veterans Affairs software program that provides detailed information on inpatient and outpatient medications. Final outcome is a percentage (0-100%) of days covered during 90-day period.	Assesses adherence via 90-day refill patterns (does not require active participation)		x	x	x	x	x
Peoplechart Meds Incontext (non-Veterans)	Private software program that uses refill data directly from retail pharmacies and Personal Benefits Manager. Final outcome is a percentage (0-100%) of days covered during 90-day period.	Assesses adherence via monthly refill patterns (does not require active participation)		x	x	x	x	x

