### Aims

The proposed research study, Mobile4Meds, seeks to determine whether text messaging or a mobile app (compared with an educational website control provided to all Veterans) can improve adherence to antiplatelet therapy among patients post-ACS/PCI. There are three topics and aims of this proposed study. First, using *Text Messaging* we aim to determine preferences for content and frequency of text messaging to promote medication adherence. Second, using *Mobile Apps* we aim to identify the most patient-centered (user-friendly, engaging, personalized) mobile app that promotes medication adherence with stratification by low/high mobile phone use and sex. Finally, we aim to examine *Medication Adherence* by comparing adherence to antiplatelet medications upon hospital discharge from ACS/PCI via: (1) text messaging, (2) mobile app, or (3) website-control. Figure 1 illustrates the aims, objectives, and outcomes of the proposed research study. Our long-term goal is to conduct a multi-site full scale RCT to determine clinical outcomes of emergency department utilization, rehospitalization, and cardiovascular (and all-cause) morbidity and mortality.

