### Aim 3: Medication Adherence Randomized Controlled Trial

#### Design

The research design for Aim 3 is an RCT that lasts 12 months. In contrast to Aims 1 and 2 that included participants who were post-ACS/PCI within one year and recruited from a cardiac rehabilitation program, participants for Aim 3 will be recruited from the hospital after ACS/PCI.

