#### Primary Statistical Analysis

Our primary analysis will use a mixed-effects linear model. The predictors will be a categorical predictor of group (with control as reference), time, and the group-by-time interactions, as well as the recruitment site (SFVAMC vs JMMC), as randomization is stratified by site. The parameters in the group-by-time interaction are the primary parameters of interest, describing whether adherence changes differentially over baseline in each of the treatment groups compared to the control group. We will also investigate whether other models for change over time are more appropriate, including arbitrary means or nonlinear time functions through comparison of Akaike information criterion/Bayesian information criterion. Secondary analyses will adjust for select covariates that are strongly associated with adherence.

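### Month-0 MMAS-8 and 7-day recall are scheduled as the first point of an outcome series, but in inpatients newly prescribed the drug they cannot measure self-managed antiplatelet adherence

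*Protocol article*

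**What the plan says.** Table 2 (Baseline Data Collection) lists MMAS-8 and 7-day recall among the secondary endpoints and marks both at months 0, 1, 6 and 12. MMAS-8 is described as "Eight-item Morisky Medication Adherence Scale (MMAS-8) self-reported questionnaire on adherence behavior for a range of scores 0-8". The recall measure is "One item asking how many days in the past week patient remembered to take medications", converted to a percentage. MEMS and both refill measures have no month-0 mark.

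The text above Table 2 names the baseline questionnaires as "1) sociodemographic information and medical history, (2) mobile phone use, and (3) Mini-Cog Test [39". Neither self-report adherence scale is in that list, so their month-0 use appears only in the table.

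For Aim 3, the Design section says that "participants for Aim 3 will be recruited from the hospital after ACS/PCI". Settings and Recruitment says: "We will recruit from SFVAMC and JMMC inpatient units using two recruitment strategies". The Sample section requires "2) recent ACS or PCI within one week, and (3) new antiplatelet (thienopyridine) prescription". The Aims section gives the target as "comparing adherence to antiplatelet medications upon hospital discharge from ACS/PCI".

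Primary Statistical Analysis names the group-by-time interaction as the parameter of interest, "describing whether adherence changes differentially over baseline in each of the treatment groups compared to the control group". The Medication Adherence section names the two self-reports as secondary outcomes and gives no separate longitudinal model for them.

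**The concern.** One schedule row implies one quantity measured repeatedly. Here month 0 and the later visits measure different things. From month 1 a patient can report on taking the antiplatelet at home. At month 0 that behaviour has not begun, so the answer must concern earlier medicines or doses given in hospital. A patient on no earlier medicines has no meaningful answer, yet the recall outcome is defined as a percentage from 0 to 100.

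Two things are at stake. A within-arm trajectory from month 0 to month 1 would mix a change of drug and setting with behaviour. And if month 0 is subtracted, or serves as the reference visit in a group-by-visit interaction, a score only weakly related to later antiplatelet adherence adds noise to the contrast.

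**Working it through.** **1. The recall window.** Suppose the index event was k days before enrolment, with k between 0 and 7. Of the 7 recalled days, 7 − k precede the event, when the drug had not yet been prescribed for it. The other k days follow the event and, for a patient still in hospital, are inpatient days. Self-managed antiplatelet days are then 7 − (7 − k) − k = 0. That month 0 is completed in hospital is inferred from inpatient recruitment and data collection after consent; the article does not state it outright.

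**2. MMAS-8.** The article gives this scale no recall window and does not show its items. Step 1 therefore does not transfer directly. The weaker argument is that a new prescription leaves no self-managed history with this drug to report.

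**3. The plan's own power figure, for scale.** 225 × 0.85 = 191.25, taken as 192, or 64 per group. With a two-sided alpha of 0.05 (assumed, since none is stated), three groups and 189 degrees of freedom, the simulated Dunnett critical value is 2.22. With a half-SD effect in both treatment arms, the power for at least one significant contrast is 86.3%, which reproduces the stated 86%. For one specified arm it is about 73%.

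**4. Precision of a change-type contrast.** Assume equal variances and correlation r between month 0 and follow-up.

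- Change score: variance = 2(1 − r) × variance of the follow-up score, so the standard error ratio is √(2(1 − r)).
- Covariate adjustment: standard error ratio is √(1 − r²).
- Power for a specified arm, normal approximation: Φ(0.5 / (ratio × √(2/64)) − 2.22). Since √(2/64) = 0.177, follow-up alone gives Φ(2.83 − 2.22) = 73%.

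| r (assumed) | Change-score SE ratio | Power, change | Power, month 0 as covariate |
|---|---|---|---|
| 0 | 1.41 | 41% | 73% |
| 0.2 | 1.26 | 51% | 75% |
| 0.3 | 1.18 | 57% | 77% |
| 0.5 | 1.00 | 73% | 85% |
| 0.7 | 0.77 | 92% | 96% |

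The penalty disappears at r=0.5 and becomes a gain above it. Covariate adjustment is never worse than follow-up alone in this table. The half-SD effect is borrowed from the sample-size section to illustrate; the article does not claim it for these scales.

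**5. If the parameter is a linear slope.** Let an effect δ be present at month 1 and sustained to month 12.

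- Months 0, 1, 6, 12: mean 4.75 and Sxx = 181 − 4 × 4.75² = 90.75. The fitted difference in slope is δ(−3.75 + 1.25 + 7.25)/90.75 = 0.052δ per month.
- Months 1, 6, 12: mean 6.33 and Sxx = 181 − 3 × 6.33² = 60.67 (unrounded mean). The fitted difference in slope is 0.

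Dropping month 0 while keeping the slope as the parameter would therefore miss a sustained effect, so the parameter must change along with the schedule.

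**The case against.** The case on the other side has several sound parts.

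- **Bias.** Month 0 precedes the intervention, so its expected score is the same in all arms, and a shift from the change of drug or setting is common to all three. A reader might infer that the arm comparisons are biased or that the self-report results as a whole are uninterpretable. The documents do not support that: between-arm contrasts at months 1, 6 and 12 stay valid.
- **The model.** The wording about change over baseline stands under the primary analysis, whose MEMS outcome has no month-0 value. A reader might infer that the article commits these two scales to change from month 0. It does not say so. Applying that model to them is an inference, though a natural one: they are the only adherence measures with a month-0 value and no other longitudinal model is given.
- **What the items refer to.** Both are described in terms of medications or adherence behaviour in general. Read that way, month 0 is an ordinary descriptor of prior medication-taking, and exact item stems may sit in the full protocol. This stands as a reason to keep the month-0 questionnaires, but not to place them as the first point of an outcome series whose target is antiplatelet adherence after discharge.
- **The size.** The 41% and 18% figures need a change-type contrast and a low r. With independent errors, a linear slope over all four visits is estimated more precisely with month 0 (Sxx 90.75 against 60.67). This also stands, so the loss is conditional.

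**Conclusion.** The point holds as a limited one on two secondary endpoints. The schedule, the inpatient setting, the one-week limit and the new prescription are all stated. Together they mean that the month-0 7-day recall is not self-managed antiplatelet adherence, and the same is probable for MMAS-8. Within-arm change from month 0 therefore cannot be reported as change in antiplatelet adherence.

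The precision loss is conditional on a change-type contrast and on r below 0.5: about 41% on the standard error at r=0, 18% at r=0.3, none at r=0.5. The documents give no value for r. The primary MEMS endpoint and the validity of the randomized comparisons are not affected.

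**What to change.** - In Table 2, label the month-0 MMAS-8 and 7-day recall as general medication adherence before this admission, with a not-applicable option for patients on no medicines. Use them as baseline covariate and descriptor, not as outcome values.
- Start the outcome series for both scales at month 1.
- In the analysis section, state that for these two scales the parameter of interest is the baseline-adjusted group difference at months 1, 6 and 12, or averaged over them, rather than the group-by-time slope alone. Without this last change, the later start would hide an effect already present and sustained from month 1.

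The cost is a table note, the item instruction at month 0 and a short analysis statement. It needs no extra visit or participant. No within-patient change from month 0 can be reported for these scales, and patients on no prior medicines need a missing-covariate category in the model.
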